## Abstract

**Introduction:**

Cardiometabolic diseases are rapidly becoming primary causes of death in developing countries, including Ghana. However, risk factors for these diseases, including obesity phenotype, and availability of cost-effective diagnostic criteria are poorly documented in an African-ancestry populations in their native locations. The extent to which the environment, occupation, geography, stress, and sleep habits contribute to the development of Cardiometabolic disorders should be examined.

**Purpose:**

The overall goal of this study is to determine the prevalence of undiagnosed diabetes, prediabetes, and associated cardiovascular risks using a multi-sampled oral glucose tolerance test. The study will also investigate the phenotype and ocular characteristics of diabetes and prediabetes subgroups, as well as determine if lifestyle changes over a one-year period will impact the progression of diabetes and prediabetes.

**Methods and analysis:**

The study employs a community-based quasi-experimental design, making use of pre- and post-intervention data, as well as a questionnaire survey of 1200 individuals residing in the Cape Coast metropolis to ascertain the prevalence and risk factors for undiagnosed diabetes and prediabetes. Physical activity, dietary habits, stress levels, sleep patterns, body image perception, and demographic characteristics will be assessed. Glucose dysregulation will be detected using oral glucose tolerance test, fasting plasma glucose, and glycated hemoglobin. Liver and kidney function will also be assessed. Diabetes and prediabetes will be classified using the American Diabetes Association criteria. Descriptive statistics, including percentages, will be used to determine the prevalence of undiagnosed diabetes and cardiovascular risks. Inferential statistics, including ANOVA, t-tests, chi-square tests, ROC curves, logistic regression, and linear mixed model regression will be used to analyze the phenotypic variations in the population, ocular characteristics, glycemic levels, sensitivity levels of diagnostic tests, etiological cause of diabetes in the population, and effects of lifestyle modifications, respectively. Additionally, t-tests will be used to assess changes in glucose regulation biomarkers after lifestyle modifications.

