### Population

The population comprises adults aged between 25 and 70 years living in households within the Cape Coast metropolis. The choice of this age range was influenced by the fact that they are at a higher risk of developing diabetes in the metropolis (41, 42). It is estimated that the number of people between the ages of 25 and 70 living in the Cape Coast Metropolis is 102,533 (43), spread across several households and communities in the metropolis. The sample for the study is being drawn from rural, peri-urban, and urban communities in the Cape Coast Metropolis. Owing to the heterogeneous nature of the Cape Coast population, the selection of participants for this study is based on different characteristics. These characteristics includes the type of community (rural, peri-urban, urban), main economic activity (farming, fishing, trading, formal work), dominant religion (Christianity, Islam, African traditional religion), and ethnicity (Fante, Ewe, Asante, northern tribes).

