### Participants

Following the protocol of the Research on Obesity and Diabetes among African Migrants (RODAM) study, which focused on obesity and type 2 diabetes among African migrants (44), this study estimates the prevalence of undiagnosed type 2 diabetes (T2D) in the Cape Coast metropolis of Ghana, at 6-7%, and the prevalence of obesity at 17%. The study aims for a power of 0.90 with α=0.05, including the Bonferroni correction. Using these parameters, a sample size of approximately 1000 would be sufficient to detect a 10% proportion of undiagnosed T2D. In order to compensate for attrition, the study seeks to recruit 1200 self-identified healthy individuals from 13 urban and rural communities in the Cape Coast Metropolis, who have not been previously diagnosed of diabetes or prediabetes prior to the study for collection of baseline data.

Due to the large and geographically dispersed population, a multistage sampling technique would be employed to sample participants for this study. This will be done in three stages, where the first stage involves dividing the population into clusters, based on the already existing communities within the metropolis. The second stage involves sampling these clusters to be used in the study by using systematic random sampling. At this stage, 13 clusters representing 13 rural, peri-urban and urban communities would be selected for the subsequent sampling stage. Finally, the third stage would involve further sampling within each selected cluster to randomly select households, and recruit the first two persons from each family line (with random replacement) in the indigenous communities, while using convenience sampling in non-indigenous communities. It is envisaged that approximately 90-100 participants will be randomly selected from three rural communities (Efutu Mampong, and Efutu), four fishing communities (Abekam, Duakor, Ekon, and Ntsen), three peri-urban communities (Ayeko-Ayeko, Ankaful and Nkanfoa) and one urban community (UCC), two market communities (Kotokuraba and Abura Markets), and one artisanal community (Siwdu). Household mapping will be done utilizing the 2021 Housing Census Data. All the 1200 volunteers will be recruited from their communities of origin before disclosing any monetary benefits.

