### Data analysis

For the accuracy of data and information, data collected through the Kobo Collect toolbox application will be downloaded into an Excel spreadsheet and screened visually and statistically. Data will be analyzed and interpreted by the principal investigator and his local collaborators and shared back with foreign collaborators. In the attempt to make the findings of the study public, data analysis will be conducted using STATA 16 and SPSS 23. Statistical tools specific and relevant to the research questions and hypotheses of the CarMeR study would be used. To determine the prevalence of undiagnosed diabetes, prediabetes and other associated cardiovascular risks, data on OGTT, FPG and HbA1c will be analyzed using descriptive statistics (percentages and confidence intervals). In order to investigate the differences in phenotype, diabetes, prediabetes, and normoglycemic groups will be compared based on BMI and body composition (waist hip ratio, body fat percentage, skeletal muscle, total body water) using analysis of variance (ANOVA) and t-test. To profile the ocular characteristics and complications of the diabetes and prediabetes groups, a cross-tabulation and a subsequent chi-square test will be done to assess the association between glycemic dysregulation and the presence of ocular complications (diabetic retinopathy, cataract, macular edema). For the purpose of ascertaining whether the predominant etiological factor of undiagnosed diabetes in this populations is insulin resistance or beta-cell failure, a homeostasis model analysis of beta [HOMA-β and HOMA-IR] will be computed and logistic regression will be used to determine the dominant factor. As a way of determining the sensitivity of other diagnostic alternatives (FPG and HbA1c) in comparison to the multi-sampled OGTT, receiver-operated characteristics (ROC curves), including sensitivity and specificity curves, will be used. Finally, to ascertain whether lifestyle changes (food choice, physical activity, weight loss, psychosocial counseling) over a one-year period impacts biomarkers of glucose regulation, a linear mixed model regression analysis, controlled for baseline characteristics will be used. T-tests will be conducted to observe changes in glucose regulation biomarkers.

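### Prevalence is planned as percentages with no age-sex standardisation named, while recruitment leaves the age-sex mix uncontrolled, so a crude figure may not represent metropolis adults aged 25-70

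*Protocol article*

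**What the plan says.** The analysis of objective 1 appears twice in the protocol article. The abstract (Methods and analysis) says: "Descriptive statistics, including percentages, will be used to determine the prevalence of undiagnosed diabetes and cardiovascular risks". The Data analysis section is fuller and is the better anchor: "data on OGTT, FPG and HbA1c will be analyzed using descriptive statistics (percentages and confidence intervals". Neither place mentions weighting, standardisation or age-specific reporting. The same section does adjust the one-year lifestyle analysis for baseline characteristics.

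The target is set under Population: an estimated 102,533 adults aged 25 to 70 in the metropolis. On the age range it says: "The choice of this age range was influenced by the fact that they are at a higher risk of developing diabetes in the metropolis". The characteristics listed there to guide selection are community type, economic activity, religion and ethnicity. Age and sex are not among them.

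Recruitment is described in several places:

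- **Participants:** "the study seeks to recruit 1200 self-identified healthy individuals from 13 urban and rural communities in the Cape Coast Metropolis", at roughly 90-100 per community. Households are chosen at random. The first two members of each family line are then taken in indigenous communities, and convenience samples are used elsewhere. "Household mapping will be done utilizing the 2021 Housing Census Data".
- **Data collection procedures:** adults aged 25 or over are picked at random within each household.
- **Questionnaire/survey questionnaire:** volunteers come from communities, markets, churches and schools.
- **Enrollment visit:** gatekeepers bring community members together, and participants arrive at 6:30am for about four hours.

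No quota or stratum for age or sex is given in any of these.

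**The concern.** A crude percentage estimates the population prevalence only if the sample has the population's mix of whatever drives prevalence. Undiagnosed diabetes may well vary with age within 25-70, and perhaps with sex. Taking whoever comes first in a family line, convenience sampling and volunteering can each favour some ages or one sex. If so, the headline figure partly describes who came. The simple confidence interval does not show this, and a larger sample does not reduce it.

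This is separate from how communities of different size are combined. With perfect community weights, the crude figure would still follow the age and sex of the attenders within each community. What is at stake is the main descriptive result: a figure above or below the planning value of 6-7% could partly reflect an older or younger sample.

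**Working it through.** **The plan's own figure.** The Participants section says "a sample size of approximately 1000 would be sufficient to detect a 10% proportion of undiagnosed T2D", with power 0.90, α = 0.05 and a Bonferroni correction. The null value, the sidedness and the number of comparisons are not stated. Taking 7% against 10%, two-sided, with two comparisons (z = 2.241 and 1.282):

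n = (2.241·√(0.07·0.93) + 1.282·√(0.10·0.90))² / 0.03² ≈ 1017

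So about 1000 can be reproduced, though other choices also come near it. This supplies the sample sizes used below.

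**Precision of a crude percentage.** Half-width = 1.96·√(p(1−p)/n). At p = 6.5%:

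- n = 1200: 1.39 points
- n = 1000: 1.53 points
- n = 1200 with an assumed design effect of 1.5 or 2: 1.71 or 1.97 points

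**Shift from the age mix.** Shift = Σ (sample share − population share) × age-specific prevalence. The article gives none of these inputs, so all are assumed:

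- Population shares at 25-34, 35-44, 45-54 and 55-70: 42/27/17/14%.
- Sample shares: mild skew 36/26/20/18, moderate 30/25/23/22, strong 22/23/26/29.
- Relative prevalence across the four bands: as in the table, scaled to 6.5% overall.

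Worked example, gradient 1:2:3:4. The base rate is 6.5/(0.42 + 0.54 + 0.51 + 0.56) = 6.5/2.03 = 3.20%. The mild-skew shift is 3.20 × (−0.06 − 0.02 + 0.09 + 0.16) = 0.54 points.

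| Relative prevalence | Mild | Moderate | Strong |
|---|---|---|---|
| flat | 0 | 0 | 0 |
| 1:1.4:1.8:2.2 | 0.31 | 0.63 | 1.09 |
| 1:2:3:4 | 0.54 | 1.09 | 1.89 |
| 1:2.5:4.5:6 | 0.70 | 1.40 | 2.42 |

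Against 1.39 points, and leaving the flat row aside, the ratios run 0.2-0.5 (mild), 0.45-1.0 (moderate) and 0.8-1.7 (strong). Against 1.71 points (design effect 1.5), only the two largest entries exceed the half-width. Against 1.97 (design effect 2), only the largest does. None reaches the full interval width of 2 × 1.39 = 2.8 points.

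**A second set of assumptions.** Take prevalence of 3%, 8% and 14% at 25-39, 40-54 and 55-70, with population shares 52/30/18.

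- True value: 0.52·3 + 0.30·8 + 0.18·14 = 6.48%.
- Attenders 45/33/22: 7.07% (+0.59).
- Attenders 35/35/30: 8.05% (+1.57).
- Attenders 60/27/13: 5.78% (−0.70).

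Only the stronger older skew passes the 1.53-point half-width at n = 1000, and only just. A younger sample moves the figure down.

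**Sex alone.** Assume 70% women in the sample against 50% in the population, and a prevalence ratio of 1.2-1.5. The shift is 0.2-0.5 points, below the half-width.

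**Cost of standardising.** The Kish variance factor, Σ (population share)²/(sample share), for the 35/35/30 example is 0.52²/0.35 + 0.30²/0.35 + 0.18²/0.30 = 0.773 + 0.257 + 0.108 = 1.14. That multiplies the half-width by √1.14 = 1.07. In the four-band scenarios at n = 1200, the standardised half-width runs from 1.31 to 1.59 points against 1.39 crude. The 1.59 arises with a flat gradient and strong skew, where standardising gains nothing.

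**The case against.** The best defence is that the text never says crude or unweighted. The abstract sentence is not exclusive, and a standardised prevalence is also a percentage with an interval. An article may leave weighting to the full protocol or analysis plan, neither of which is shown. This stands to the extent that silence alone would not be a finding. The point rests on the named method taken together with the stated recruitment.

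Second, households are chosen at random after census-based mapping, and adults are to be picked at random within them, which tends to reproduce the age-sex mix. A reader might infer that nothing protects the mix; the article does not support that. But the protection is partial. Random picking sits uneasily with taking the first two of a family line, cannot apply to convenience samples, and does not address who attends. No passage says that attendance differs by age.

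Third, the reason given for the age range might be read as evidence of an age gradient. It compares ages 25-70 with other ages and shows no gradient inside the range.

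Fourth, the size is assumed. In the stronger three-band example, the interval reported around 8.05% at n = 1000 would be ±1.69, or 6.36-9.74%, which still contains 6.48%. All of this stands.

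**Conclusion.** The concern holds in a limited form. The stated analysis is percentages with intervals, no age-sex standardisation is named, and part of the recruitment leaves the age-sex mix uncontrolled. A crude percentage may therefore not represent metropolis adults aged 25-70.

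Under the assumed rates at 6.5% prevalence, the shift is about 0.3-0.7 points for a mild skew and about 0.6-2.4 points for a moderate to strong one, against a simple-random half-width of 1.4-1.5 points. It is zero if prevalence is flat across age, and relatively smaller with clustering.

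Three stronger readings are not supported:

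- **That the shift matches the whole confidence interval.** At 6.5% it does not in any scenario tried; the comparison is with the half-width, and only at the upper end.
- **That it would produce a false finding against 7%.** The Data analysis section plans estimation, with no such test, and 6-7% is the study's own planning estimate for the metropolis.
- **That standardising would make the result comparable across countries.** A metropolis standard does not do that; a common standard population would be needed.

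**What to change.** In the Data analysis section, with the abstract to match, state that prevalence of undiagnosed diabetes, prediabetes and each cardiovascular risk will be post-stratified by age band and sex to the 2021 census population of the metropolis aged 25-70, with a confidence interval for that estimate. Report the crude percentage and the age- and sex-specific percentages beside it.

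Add two limits. First, the estimate applies to adults who meet the exclusion criteria (which remove, among others, pregnant and breastfeeding women, people with anaemia and users of cholesterol medication), so the census mix is only an approximate standard for them. Second, it corrects for age and sex only, not for other volunteer bias.

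The cost is small. Demographic data are already collected and age is an eligibility criterion. The interval may widen slightly (variance factor about 1.14 in the stronger three-band example). Age-by-sex census counts must be obtained, since the article cites the 2021 census only for household mapping. The change is best made before the prevalence data are analysed.

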**Ethics and dissemination:**

Ethics approval was granted by the Institutional Review Board of the University of Cape Coast, Ghana (UCCIRB/EXT/2022/27). The findings will be disseminated in community workshops, online learning platforms, academic conferences and submitted to peer-reviewed journals for publication.

## Introduction

Research has established that obesity, high levels of glucose, and triglycerides are significant contributors to the risks of developing cardiometabolic diseases [CMDs] (1–4). However, literature suggests that two-thirds of African-born individuals in sub-Saharan Africa living in America diagnosed with abnormal glucose tolerance are more likely to be non-obese (5). This has led to research to establish the specific causes of diabetes and prediabetes in an African population, and to identify risk factors unique to Africans. The main mechanisms for the development of diabetes are beta-cell failure and insulin resistance, with abnormal glucose tolerance representing an imbalance between the degree of insulin resistance and the β-cell secretion (6–8). Identifying the etiology of diabetes is critical for prescribing the relevant treatment or interventions (6).

Globally, 537 million adults live with diabetes, with Africa contributing 4.47% (24 million) and witnessing 416,000 diabetes-related deaths in 2021 alone (9). According to the International Diabetes Federation (9), this prevalence is projected to double by 2045 due to high rates of abnormal glucose tolerance, including prediabetes (5, 10–12). Prediabetes and diabetes represent a glycemic continuum with both associated with vascular complications and an increased burden on all-cause mortality rates. Presently, 179.2 million individuals globally with undiagnosed diabetes (13), with the IDF Africa Region standing out with the highest rate of undiagnosed cases among all IDF regions, at 60% (14). This underscores the critical need for increased awareness, early detection, and intervention strategies to address undiagnosed diabetes in Africa.

Many pathways contribute to abnormal glucose tolerance, and predisposing factors can differ among populations (8, 15). Although there is data on diabetes in populations of African descent, such as African Americans and African-Caribbean’s (15),, these data cannot be used to infer about African-born individuals in the sub-Saharan Africa. There have been divergent views on the major contributor to abnormal glucose intolerance, with a study (7) proposing beta-cell failure, and other studies (6, 8) implicating insulin resistance. This highlights the importance of conducting studies within diverse Sub-Saharan African populations to identify population-specific risk factors. Additionally, with increasing physical inactivity, consumption of high energy-dense foods, social alcohol drinking, and the sedentary lifestyle of Africans living in Africa (16), assessing risks for cardiometabolic diseases and promptly provide health promotion interventions is relevant.

Diabetes poses a significant challenge to global public health and its burden doubled with the emergence of the COVID-19 pandemic. In Africa, most COVID-19 deaths were significantly associated with underlying health conditions, including diabetes and other cardiovascular disease risks. A systematic review established that diabetes mellitus was associated with higher COVID-19 mortality rates in sub-Saharan Africa (17). The findings indicated a statistically significant association between diabetes mellitus and increased mortality among COVID-19 inpatients, showing a 1.39-fold higher risk of death in patients with diabetes mellitus compared to those without.

Notwithstanding, there is still a dearth of accurate and revealing data on the prevalence of diabetes and other cardiovascular and metabolic disease (CMD) risks in sub-Saharan Africa. This study seeks to establish knowledge about the prevalence of diabetes and other CMD risks, to reduce diabetes prevalence and prepare for potential future pandemics. More than 75% of the countries in sub-Saharan Africa lack contemporary primary data on diabetes prevalence (18), with estimates in the sub-region relying on data extrapolation and mathematical modeling. However, consolidating data from the various countries within sub-Saharan Africa would help facilitate the collection of more comprehensive information regarding the etiology and presentation of abnormal glucose tolerance in the sub-region. By doing so, Africa can gain a more accurate understanding of its diabetes burden and risk factors, enabling proactive measures to reverse the trajectories of the diabetes epidemic projected by the IDF for 2045 through early detection and diagnosis.

Early diagnosis of diabetes is crucial for mitigating its debilitating effects, including peripheral neuropathy, retinopathy, diabetic foot complications, and the susceptibility to infectious diseases (17, 19, 20). The estimated prevalence of diabetes in Ghana is 6.5% (21), suggesting that one in every 15 Ghanaians has diabetes, signifying the onset of a worrying epidemic. Diabetes is a major contributor to mortality in Ghana, with 9,778 deaths reported in 2017, up from the 8528 in 2014 (22). The cost of treating one person with diabetes in Ghana as at 2017 was a high $106.5. Diabetes is reaching epidemic proportions in sub-Saharan Africa, with the region experiencing the most rapid increase in type 2 diabetes (T2D) worldwide and the highest proportion undiagnosed diabetes (9). To address this epidemic and its complications, comorbidities and mortalities, measures must encourage the early diagnosis of diabetes and reduce undiagnosed diabetes (9). Identifying and developing African-specific tools and interventions to improve the early diagnosis of diabetes and prescribe effective treatments requires more clinical research in the African population. The prospective findings of this research should be incorporated into the clinical care of prediabetes and diabetes, and replicated across many African countries in both rural and urban areas. Given that Ghana has a typical African population and an epidemic-like prevalence of diabetes (21), data from this study can bridge developing and developed countries, increasing the degree of certainty of data extrapolation and modeling of diabetes-related prevalence and outcomes.

The increased susceptibility to diabetes in people from lower- and middle-income countries has been well explored (9, 23–25). In Ghana, the extent to which obesity phenotypes, dietary habits, socioeconomic status, perceived stress, sleep patterns, geographical location, and occupational characteristics contribute to cardiometabolic risk development has not been well explored (26–30), especially due to diagnostics and methodological limitations. There is still a dearth of data concerning the actual prevalence of undiagnosed diabetes in Ghana, the specific interventions to remedy these risk factors, and how culturally sensitive non-pharmacological interventions such as diet and physical activity can contribute to diabetes remission in newly diagnosed persons with abnormal glucose tolerance.

Non-African studies have shown the possibility of diabetes and prediabetes remission through non-pharmacological interventions (31, 32), making it important to replicate and improve on these studies in a typical African-born population. Although some studies from developed countries have shown lifestyle changes to significantly influence diabetes remission (33–36), no prospective study done in sub-Saharan Africa and Ghana has shown the possibility of people newly diagnosed with diabetes reverting to prediabetes or people with prediabetes reverting to normal glucose tolerance through non-pharmacological lifestyle interventions. These reasons, as well as the high prevalence of undiagnosed diabetes and the projected increase of 143% by 2045, have necessitated the inception and execution of this project. This project assesses the role of lifestyle choices, environmental exposures, psychosocial factors and nutrition on the prevalence of obesity, hypertension and diabetes (CMD risk factors) among Ghanaians, and how these contribute to improved health and visual outcomes.

Due to the demographic characteristics and nature of diabetes, the biopsychosocial model of disease development underpins the CarMeR Study. The model as utilized in a previous study, propounds that disease occurrence results from the interplay of biological, psychological and social factors (37). It explains how factors, including biological factors (family history diabetes, sex), sociological factors (familial, occupation, economic status, nutrition, ethnicity, place of birth and early life experiences), and psychological factors (stress and sleep patterns) contribute to disease development. The biopsychosocial model suggests that each of these three domains has an influence on health. The biopsychosocial model has been selected because it provides a framework for understanding risk factors associated with CMDs in Ghana. As illustrated in **Figure 1**, we hypothesize that genetic factors, social factors, familial factors, stress, economic status, religion, ethnicity, nutrition patterns, physical activity and other population characteristics play a crucial role in determining an individual’s susceptibility to CMDs. Incorporating these factors into our conceptual model, we envisage gaining a deeper understanding of the complex interactions that contribute to the risks of CMDs such as diabetes, obesity, hypertension, and other cardiovascular diseases. This model will explore the prevalence of undiagnosed diabetes, prediabetes and hypertension among critical populations in Ghana, and how various factors predispose individuals to risk of cardiometabolic diseases.

